### Study withdrawals

Patients will be permitted to request withdrawal from treatment at any time without providing reasons. The primary investigator and the attending physician will also have authority to drop patients from the trial treatment if it is considered that further participation in the trial would be detrimental to the patient's well-being. Such treatment withdrawals will be documented using a case report form and in patient's medical records. In addition, we have a plan to evaluate the results of this trial in the middle of this study, and based on these interim results the trial can be prematurely terminated if the drug effect would be highly suggested to be beneficial or harmful.

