### Blinding

Study patients, interviewers responsible for administering questionnaires, inspectors that conducted echocardiography and cardiopulmonary exercise tests (CPETs), and the study investigators and directors will be blinded from details of the randomization. Unblinding will be only accepted by the independent data and safety monitoring committee when a serious adverse event occurs, upon request from regulatory authorities, or when information regarding the allocation procedure is deemed important from the perspective of patient safety.

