### Sample size calculation

Several studies have investigated the therapeutic efficacies of PDE5 inhibitors (the majority employed sildenafil as a study drug) in patients with chronic SHF [10,22]. Most clinical trials have adopted maximal V_O2_ to calculate the sample size and statistical power. In a study of 34 patients with SHF and pulmonary hypertension, Lewis and colleagues reported a 14% increase in maximal V_O2_ by sildenafil administration (from 12.2 ± 0.7 to 13.9 ± 1.0 ml/g/minute) [10]. On the other hand, in a study investigating the efficacy of sildenafil in 23 patients with SHF, Guazzi and colleagues reported an increase in maximal V_O2_ of approximately 21% (from 12.9 ± 6.8 to 15.6 ± 6.0 ml/minute/kg) [22].

Assuming a mean baseline maximal V_O2_ of 14.0 ml/kg/minute, a percentage increase in maximal V_O2_ of 0% in the placebo group and 15% in the udenafil group (data taken from the study by Lewis and colleagues [10] and our previous experiences), we anticipate final maximal V_O2_ values of 14.0 ml/kg/minute in the placebo group and of 16.1 ml/kg/minute in the udenafil group, with a conservative standard deviation for mean maximal V_O2_ of 2.5 ml/kg/minute. Accordingly, we calculated the sample size assuming a standard deviation of 2.5 ml/kg/minute using the following formula:

$$n_{i}=\frac{2{\left(Z_{a/2}+Z_{\beta }\right)}^{2}\sigma^{2}}{{\left(\mu_{1}-\mu_{2}\right)}^{2}}$$

Based on these assumptions and calculations, detection of the 15% increase in maximal V_O2_ by udenafil, with a power of 80% and a statistical significance level of 5%, will require 23 patients per group for a standard deviation of 2.5 ml/kg/minute. Thus, allowing for a loss of 10% (data are missing completely at random, which implies that the missing data are unrelated to the study variables), a maximum of 52 patients would be required or 26 patients per group.

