### Statistical considerations

The principal analysis will be conducted on an intention-to-treat basis. We will analyze all patients according to the randomization scheme. However, data that are missing completely at random will be omitted without analysis. The differences between the treatment groups in the main outcome will be assessed using an unpaired *t* test adjusted by baseline values (analysis of covariance). Binary endpoints will be compared using Fisher’s exact probability test. For survival analysis and clinical events, Kaplan–Meier survival curves will be plotted and compared using the log-rank test based on a proportional hazards model using the chi-square test. Statistical significance will be accepted for *P* <0.05.

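### A mid-trial stop for benefit is combined with a sample size and a final P<0.05 that make no allowance for it, so the rules as written do not hold the 5% level

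*Protocol article*

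**What the plan says.** Three parts of the protocol article bear on this point.

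- **Study withdrawals** announces the look: "we have a plan to evaluate the results of this trial in the middle of this study". It then gives the consequence: "based on these interim results the trial can be prematurely terminated if the drug effect would be highly suggested to be beneficial or harmful". Because benefit is named, this is an efficacy look as well as a safety review. No endpoint, number of patients or numerical criterion is attached to it.
- **Sample size calculation** uses the standard fixed-sample formula for two means with a two-sided critical value. It assumes final means of "14.0 ml/kg/minute in the placebo group and of 16.1 ml/kg/minute in the udenafil group" and a standard deviation of 2.5, and concludes that the design, "with a power of 80% and a statistical significance level of 5%, will require 23 patients per group", becomes 26 per group after a 10% allowance for loss.
- **Statistical considerations** closes with one threshold for all tests: "Statistical significance will be accepted for *P* <0.05".

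The Blinding section says that "the study investigators and directors will be blinded from details of the randomization" and leaves unblinding to the independent data and safety monitoring committee. The Safety section gives that committee a safety-monitoring role. Neither section gives it the efficacy look.

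**The concern.** A trial that can be declared positive at an interim look, and otherwise goes on to a final test at the full 5%, has two opportunities for a false-positive result. The final test alone already uses the whole 5%, so any chance of a false stop for benefit is added on top. The stated significance level would then not be the true one for the primary outcome, the change in maximal oxygen uptake.

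The criterion is also qualitative. If the threshold is settled only after the interim results are known, the error rate cannot be worked out at all, and this cannot be repaired credibly afterwards. The article gives the trial status as patient recruitment, so the time to settle the matter is before the look.

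**Working it through.** **1. The plan's own sample size.** Inputs from the Sample size calculation section: difference 16.1 − 14.0 = 2.1 ml/kg/minute, SD 2.5, two-sided 5%, power 80%.

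n = 2(1.960 + 0.842)² × 2.5² / 2.1² = 22.25, rounded up to 23 per group. With 10% loss, 23 / 0.9 = 25.6, so 26 per group and 52 in total. This agrees with the article. It is a single-test design: the critical value 1.960 belongs to the final analysis and no alpha is set aside for an interim look.

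**2. Overall type I error with one look.** Let Z₁ and Z₂ be the interim and final test statistics. Under no effect they are standard normal with correlation √t, where t is the information fraction at the look. With interim critical value c₁ and the final test left at 1.960:

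overall two-sided error = 1 − P(|Z₁| < c₁ and |Z₂| < 1.960).

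The article gives neither t nor c₁. I assume t = 1/2, with a range of 1/3 to 2/3, and vary the interim threshold:

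| Interim judged at | t = 1/3 | t = 1/2 | t = 2/3 |
|---|---|---|---|
| P<0.001 | 5.05% | 5.02% | 5.01% |
| P<0.0052 | 5.30% | 5.20% | 5.09% |
| P<0.01 | 5.64% | 5.46% | 5.26% |
| P<0.05 | 8.83% | 8.31% | 7.70% |

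Every cell exceeds 5%. The same holds for false claims of benefit alone. Against a nominal 2.5% in that tail, the figures at t = 1/2 are 2.51% (interim P<0.001), 2.73% (P<0.01) and 4.16% (P<0.05).

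These are normal-theory values. A t-test simulation with 13 and then 26 per arm, at P<0.05 on both occasions, also gave 8.3%.

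**3. Boundaries that restore 5% at t = 1/2.** Solve the same expression for 5%:

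- O'Brien-Fleming: critical values 2.797 and 1.977, so P<0.0052 then P<0.0480.
- Haybittle-Peto: 3.291 and 1.962, so P<0.001 then P<0.0498.
- Pocock: 2.178 at both looks, so P<0.0294 each time.

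**4. Power under those boundaries.** The drift at 23 per group is 2.1 / (2.5 × √(2/23)) = 2.849. The fixed design has power 81.3%. With the look it is 81.0% (O'Brien-Fleming), 81.3% (Haybittle-Peto) or 77.0% (Pocock). At 26 per group the values are 85.7% for the fixed design, then 85.5%, 85.7% and 82.0%.

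**The case against.** The strongest reply is that this is a journal article. Numerical boundaries usually sit in an analysis plan or committee charter, neither of which is shown, so their absence is no finding. The P<0.05 sentence covers every test in the paper and could be read as the overall level. The wording of the stopping criterion also suggests something stricter than ordinary significance, in which case the excess could be as little as 0.02 percentage points.

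Much of this stands. The lack of a boundary is not the complaint in itself, and the size of the excess is unknown. What remains is the combination that the article does state: a stop for benefit is allowed, the sample size spends the full 5% at the end, and the threshold is P<0.05. An unseen boundary that holds 5% would need a final level below 0.05, so the sentence in Statistical considerations would still have to be reconciled with it.

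Three stronger readings are tempting but not supported.

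- **That the true error rate is 8.3%.** This requires the interim to be judged at P<0.05. The article does not say so, and its wording points away from it.
- **That early stopping would overstate the effect by about a third, and that a formal boundary cures this.** With a true difference of 2.1, SD 2.5 and 13 per arm, the expected estimate given a stop at P<0.05 is 2.77, or 32% too high. That again assumes a P<0.05 rule. Given a stop, stricter boundaries increase the bias: to about 59% at P<0.0052 and 77% at P<0.001. They make such stops rarer but do not remove the bias.
- **That the investigators will see results by arm.** This would rest on the authors' use of the first person when they describe the look. The Blinding section keeps investigators and directors blinded. The article only leaves unsaid who does the look.

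**Conclusion.** The point holds as an inconsistency between stated rules. With a stop for benefit allowed and the final test at P<0.05, the overall type I error exceeds 5% at any interim threshold that could be crossed.

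The amount is not determined by the document. At half information it runs from 5.02% (interim P<0.001) through 5.5% (P<0.01) to 8.3% (P<0.05), and a P<0.05 look gives 7.7% to 8.8% as its timing moves from 2/3 to 1/3 of the information. These figures assume a single look, a stop for benefit counted as a positive trial, and normal theory.

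The sample size reproduces and need not change under an O'Brien-Fleming or Haybittle-Peto boundary.

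**What to change.** Before any interim data are seen, state:

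1. that there is one efficacy look, and its timing as a number of patients with a week-12 cardiopulmonary exercise test (26 of 52 would be half information);
2. a numerical boundary for benefit on the primary outcome and the matching final level, for example O'Brien-Fleming (P<0.0052, then P<0.048) or Haybittle-Peto (P<0.001, then P<0.0498). These levels are for a look at half information and must be recalculated for another timing. The choice is the sponsor's;
3. in Statistical considerations, that final level in place of P<0.05 for the primary outcome;
4. that the data and safety monitoring committee does the look, in keeping with the Blinding section, and that the review for harm is left to its safety judgement.

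**Cost.** The change is to wording. At 23 per group, power falls from 81.3% to 81.0% with O'Brien-Fleming and stays at 81.3% after rounding with Haybittle-Peto, with no extra patients. Pocock would take power to 77.0% at that size, below the planned 80%. An estimate from a trial stopped early would still be biased upward under any of these boundaries; it should be reported as such or accompanied by a bias-adjusted estimate.

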### Study endpoints

The primary outcome will be changes in maximal V_O2_ measured at baseline and at 12-week visits. Maximal V_O2_ will be defined as highest oxygen uptake (averaged over five consecutive breaths) during the last minute of symptom-limited CPET. Secondary endpoints are detailed in Table 2.

**Table 2 T2:** Secondary outcomes

	**Secondary outcomes**
1.	Changes of ventilator efficiency (V_E_/V_CO2_ slope)
2.	Ejection fraction
3.	E velocity of mitral inflow, E′ velocity, systolic mitral annular velocity (S′ velocity)
4.	E/E′ ratio
5.	Deceleration time
6.	Pulmonary artery systolic pressure measured by echocardiography at baseline and 12 weeks
7.	Post-exercise pulmonary artery systolic pressure measured by echocardiography at baseline and 12 weeks
8.	Symptomatic status (NYHA functional class and Borg dyspnea index)
9.	Plasma concentration of BNP assessed at baseline, 4 weeks, and 12 weeks
10.	Clinical endpoints, all-cause death, cardiac death, admission for heart failure, and the composites of these events will be assessed until the end of the study period
11.	Development of facial flushing, febrile sensation, eyeball pain, visual disturbance, headache, penile erection, intolerance or development of other adverse drug reactions related with study drug will be assessed

*BNP*, B-type natriuretic peptide; *NYHA*, New York Heart Association; V_E_, minute ventilation (l/minute); V_CO2_, carbon dioxide production (ml/kg/minute).

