**Methods/design:**

Stable, chronic SHF patients will be randomly assigned to placebo (26 patients) or udenafil at a dose of 50 mg twice per day (26 patients) for the first 4 weeks followed by 100 mg twice daily for the next 8 weeks. Eligibility criteria will be age ≥18 years, clinical diagnosis of chronic SHF with current New York Heart Association class II to IV symptoms, left ventricular ejection fraction ≤ 40%, and experience of at least one of following during the 12 months prior to study entry: hospitalization for decompensated heart failure, acute treatment with intravenous loop diuretics or hemofiltration, or pulmonary artery systolic pressure ≥40mmHg on transthoracic echocardiography. Pharmacological therapy for SHF will be optimized in all patients at least 30 days before study entry. The primary outcome will be the change of maximal oxygen uptake, assessed by cardiopulmonary exercise testing. Secondary outcomes will include changes in ventilatory efficiency (minute ventilation/carbon dioxide production slope), left ventricular systolic and diastolic parameters, pulmonary artery systolic pressure, plasma concentration of brain natriuretic peptide, occurrence of mortality or hospitalization for heart failure, and the occurrence of any adverse event.

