### Follow-up protocol

The trial duration is expected to be 3 months. Participants will attend study visits at screening, baseline, and weeks 4 and 12. At each visit, patients will undergo a complete physical examination, medical history-taking, and an assessment of drug compliance. Investigators will evaluate all clinical and laboratory adverse events at each visit. New York Heart Association functional class and predefined clinical events as described below will be recorded at each clinical visit. Venous blood will be drawn after a 15-minute rest period at screening, and at 4-week and 12-week visits, and will be subjected to the following test battery: B-type natriuretic peptide, complete blood count, electrolyte panel, serum creatinine, and liver function test. At screening visits, echocardiography will be performed at rest, and based on the results obtained study investigators will decide on patient eligibility. At baseline and at 12 weeks, participants will undergo CPET (V_Max_ 229 Respiratory Analyzer; SensorMedics, Homestead, FL, USA) and exercise echocardiography to evaluate exercise capacity in a quantitative manner. At all study visits, researchers will collect health-related information, such as adverse events, admission for acute decompensated HF, and change in medication. In addition, medication compliance of all participants will be carefully assessed by the pill-count method at every visit.

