### Safety

Any participants with a hypersensitivity reaction to the study drug or an adverse event after study medication, those that do not want to remain in the trial, or those that comply with medication <80% will be dropped from the trial, as will those judged to be at risk due to participation in the trial by an attending physician.

Udenafil has been reported to be safe and well tolerated by healthy volunteers [17], and by patients with erectile dysfunction [14]. No serious adverse events occurred in either study. Common adverse events included nausea, headache, facial flushing, febrile sensation, penile erection, and eyeball pain, all of which have been reported to adverse events of other PDE5 inhibitors. Adverse events will be immediately reported directly to the study investigators, and study staffs will be obligated to manage these events. Patients will be interviewed at each visit about the occurrence of any adverse events, and onset time, duration, and severity will be recorded on case report forms. The possibility of causal relationships between the study drug and the intensities of adverse events will be evaluated by the investigators. The investigators are mandated to report serious adverse events to the institutional review board within 24 hours of recognition. A data and safety monitoring committee will monitor the safety of patients participating in the trial and all ongoing serious adverse events will be closely followed until these conditions have stabilized.

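### Table 2 item 11 counts unlisted adverse events only if they are related to study drug, whereas the abstract promises any adverse event; the filter can dilute a real excess

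*Protocol article*

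**What the plan says.** All places are in the protocol article.

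- **Abstract, Methods/design.** The list of secondary outcomes ends with "and the occurrence of any adverse event".
- **Study endpoints.** "Secondary endpoints are detailed in Table 2". The table is therefore the detailed definition.
- **Table 2, item 11.** It begins "Development of facial flushing, febrile sensation, eyeball pain, visual disturbance, headache, penile erection" and ends "intolerance or development of other adverse drug reactions related with study drug will be assessed".
- **Table 2, item 10.** All-cause death, cardiac death, heart failure admission and their composites are outcomes, with no condition on cause.
- **Follow-up protocol.** "Investigators will evaluate all clinical and laboratory adverse events at each visit".
- **Safety.** "The possibility of causal relationships between the study drug and the intensities of adverse events will be evaluated by the investigators". Occurrence is asked about at each visit, and onset, duration and severity are recorded.
- **Blinding.** "the study investigators and directors will be blinded from details of the randomization".
- **Statistical considerations.** Binary endpoints are compared by Fisher's "exact probability test".

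**The concern.** The same outcome has two definitions, and an analyst cannot follow both. The abstract counts every adverse event. The table counts an event outside its named list only if it is a reaction related to the drug. Full collection of events does not settle the matter: it fixes what is recorded, not which events form the outcome to be compared.

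The events that depend on the choice are not trivial. The Safety section puts nausea first among the common adverse events of udenafil, yet item 11 does not name it. Hypotension is not named either, although the Background describes vasodilatation with the drug and Table 1 excludes patients who already have severe hypotension. Creatinine and liver tests are drawn under the Follow-up protocol, but laboratory events are not named. The earlier safety experience cited in the Safety section comes from healthy volunteers and patients with erectile dysfunction. A harm particular to heart failure patients could therefore well appear among the unlisted events, where an investigator can plausibly ascribe it to the underlying disease or to background medication.

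At stake is whether an excess of such events on udenafil would show in the between-arm comparison.

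**Working it through.** **Step 1. The two definitions, by type of event**

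| Type of event | Abstract | Table 2 |
|---|---|---|
| Death, heart failure admission | counted | counted (item 10), no judgement of cause |
| Six named reactions, intolerance | counted | counted (item 11), listed outright |
| Any other event, judged related | counted | counted (item 11, open-ended part) |
| Any other event, judged unrelated | counted | **not counted** |

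The definitions differ only in the last row. That row holds unlisted events outside item 10, such as nausea, hypotension or a laboratory abnormality, that are not attributed to the drug.

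**Step 2. Does another statement resolve the conflict?** No. The Follow-up protocol and Safety sections govern collection and recording. Apart from the abstract, nothing says that all events will be compared between arms regardless of cause.

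**Step 3. What an even-handed filter does.** The documents give no adverse-event rates, so the rates here are assumptions for illustration.

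- From the documents: 26 patients per arm (Sample size calculation), Fisher's exact test, and significance at P < 0.05 (Statistical considerations).
- Assumed: unlisted events in 50% of udenafil and 20% of placebo patients.
- Assumed: the same share q of patients with such an event has it judged related in both arms, as blinded judges would tend to produce.

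The counted rates are 0.50q and 0.20q, and their difference is 0.30q. Power is the sum, over all pairs of counts (a, b) from 0 to 26 for which the two-sided Fisher P is below 0.05, of Bin(a; 26, 0.20q) × Bin(b; 26, 0.50q).

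| q | Udenafil | Placebo | Difference (points) | Exact power |
|---|---|---|---|---|
| 1.00 (all events count) | 50% | 20% | 30 | 54% |
| 0.75 | 37.5% | 15% | 22.5 | 34% |
| 0.50 | 25% | 10% | 15 | 19% |
| 0.25 | 12.5% | 5% | 7.5 | 4% |

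The ratio of rates stays at 2.5 throughout (0.50q / 0.20q). What shrinks is the absolute difference and, with it, the chance of detecting it.

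**Step 4. The plan's own sample size.** It is not in question. With a standard deviation of 2.5 and a difference of 16.1 − 14.0 = 2.1 ml/kg/minute, the plan's formula gives 22.25, hence 23 per group. Allowing for 10% loss, 23 / 0.9 = 25.6, hence 26 per group and 52 in all, as stated. Nothing in this point changes it.

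**The case against.** The strongest reply is that this is a wording mismatch in one of eleven secondary items in a small trial. All events are collected, so no data are lost. The article is condensed, and the detail of adverse-event tables commonly sits in a full protocol or analysis plan that is not shown. No passage says outright that the causality assessment in the Safety section selects events for analysis. Most of this stands and limits the weight of the point. It does not remove it, because the point concerns two stated definitions that disagree, not a missing detail.

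A reader might also infer three stronger things that the documents do not support.

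- **That the whole safety comparison depends on a causality judgement.** It does not. Item 10 covers deaths and heart failure admissions without one, and the six named reactions are listed outright. The wording of item 11 could be stretched so that the relatedness condition governs the named reactions too, but its natural attachment is to the other reactions at the end.
- **That the filter will create a false excess on udenafil.** This needs attribution to differ by arm. The Blinding section blinds the investigators, who are the causality judges. Recognisable class effects such as flushing could hint at the arm, so differential attribution is possible, but nothing shows that it will occur. Counting all events would not fully cure it either, since patients who guess their arm may report subjective events differently.
- **That serious worsening of heart failure could vanish from the outcomes.** Item 10 prevents this for death and admission, and items 8 and 9 follow symptoms and natriuretic peptide.

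**Conclusion.** The abstract and Table 2 contradict each other on the adverse-event outcome. Because the Study endpoints section sends the reader to Table 2, the restrictive definition is the one an analyst would apply. The effect is confined to unlisted events outside item 10.

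The supportable harm is dilution. In the illustration, power falls from 54% to 34% if three quarters of the events are judged related, and to 19% if half are. These figures rest on assumed rates of 50% and 20% and on an equal related share in both arms. They show direction and rough size, and do not predict what this trial would see. Even with every event counted, power at this sample size is only moderate for a 30-point difference, so a filter that lowers it further is hard to justify when the full data are at hand. Since the events are recorded anyway, the defect can be put right without loss.

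**What to change.** Reword Table 2 item 11 so that the outcome is any adverse event and any serious adverse event, by arm, regardless of judged relation to study drug. These would be compared with the Fisher test already planned for binary endpoints. Keep the six named reactions, intolerance and the events that investigators judge related as descriptive subsets. This brings the table into line with the abstract.

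The Trial status section indicates that patients are being recruited, so the change should be made and dated before unblinding and before any interim look by arm. Otherwise the definition could be chosen with results in view.

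The cost is one table line and one more tabulation. No new data, visits or patients are needed. Counting everything does bring in events from background illness, which adds noise; the subset of events judged related keeps the narrower view available.
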